## Abstract

**Background::**

Alzheimer’s disease (AD), the most common cause of dementia, is a neurodegenerative disease resulting from extracellular and intracellular deposits of amyloid-β (Aβ) and neurofibrillary tangles in the brain. Although many clinical studies evaluating pharmacological approaches have been conducted, most have shown disappointing results; thus, innovative strategies other than drugs have been actively attempted.

**Objective::**

This study aims to explore low-dose radiation therapy (LDRT) for the treatment of patients with AD based on preclinical evidence, case reports, and a small pilot trial in humans.

**Methods::**

This study is a phase II, multicenter, prospective, single-blinded, randomized controlled trial that will evaluate the efficacy and safety of LDRT to the whole brain using a linear accelerator in patients with mild AD. Sixty participants will be randomly assigned to three groups: experimental I (24 cGy/6 fractions), experimental II (300 cGy/6 fractions), or sham RT group (0 cGy/6 fractions). During LDRT and follow-up visits after LDRT, possible adverse events will be assessed by the physician’s interview and neurological examinations. Furthermore, the effectiveness of LDRT will be measured using neurocognitive function tests and imaging tools at 6 and 12 months after LDRT. We will also monitor the alterations in cytokines, Aβ_42_/Aβ_40_ ratio, and tau levels in plasma. Our primary endpoint is the change in cognitive function test scores estimated by the Alzheimer’s Disease Assessment Scale-Korea compared to baseline after 6 months of LDRT.

**Conclusions::**

This study is registered at ClinicalTrials.gov [NCT05635968] and is currently recruiting patients. This study will provide evidence that LDRT is a new treatment strategy for AD.

## INTRODUCTION

The aging population is a global mega-trend, and the expected increase in the population with dementia places a heavy socioeconomic burden on most countries [1]. Approximately 50 million people worldwide have dementia, with nearly 10 million new cases occurring each year [1, 2]. Dementia is characterized by a marked loss of cognitive and emotional abilities and negatively affects daily functioning and activities [3, 4]. Alzheimer’s disease (AD) is the most common cause of dementia, a degenerative disease that results from extracellular and intracellular deposits of amyloid-β (Aβ) plaques and insoluble intracellular neurofibrillary tangles in the brain [5]. Despite numerous clinical studies investigating pharmacological approaches, only four drugs (donepezil, rivastigmine, galantamine, and memantine) have been available on the market to relieve symptoms in patients with AD [6]. Recently, aducanumab has been approved by U.S. Food and Drug Administration as the first mechanism-based fundamental disease-modifying drug for AD targeting Aβ plaques [7], but controversy over its efficacy continues due to ambiguous clinical results [8]. In addition, aducanumab remains inaccessible due to high burden of cost [8]. Furthermore, aducanumab has not yet been approved by the Korean Ministry of Food and Drug Safety, making it difficult for domestic patients to access it.

Meanwhile, as a non-pharmacological intervention, low-dose radiation therapy (LDRT) has gained attention after a case report described significant improvement in a patient with advanced AD who underwent computed tomography (CT) scans of the brain five times [9, 10]. Recently, several preclinical studies based on mouse models revealed a significant reduction in Aβ plaques with LDRT [11–13], and LDRT induced the upregulation of pre- and post-synaptic molecules in the brains of AD mouse models [14]. Moreover, a recent study showed that LDRT seems to reduce the levels of pro-inflammatory cytokines in animal models of AD [11, 14]; therefore, several pilot studies or clinical trials investigating the effect of LDRT on humans have been launched [15, 16]. Most recently, researchers at Virginia Commonwealth University (VCU) published positive pilot study results showing that four of five patients diagnosed with early AD experienced improved or stable cognition after treatment with LDRT [17]. However, the efficacy of LDRT has not yet been clearly demonstrated, and the optimal LDRT dose scheme for AD is still exploratory.

This study aims to explore LDRT for the treatment of patients with AD based on preclinical evidence and case reports. We will evaluate the safety and potential therapeutic effects of LDRT and explore the appropriate LDRT dose per fraction and schedule.

## MATERIALS AND METHODS

### Study design and registration

This phase II multicenter prospective randomized controlled trial will evaluate the safety and efficacy of LDRT in the whole brain of patients with AD and determine the potentially applicable radiation dose. This trial is registered on ClinicalTrials.gov [NCT05635968]. Patients who are candidates for this study will be randomized into three treatment groups at a 1:1:1: ratio: 24 cGy/6 fractions of LDRT, 300 cGy/6 fractions of LDRT, or sham RT group (Fig. 1).

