### Baseline and randomization (Visit 2)

Eligible patients will be assigned to three treatment groups (two experimental groups and one control group) by stratified block randomization using a random number table. The researcher will obtain consent and assign the screening number to each participant in order. After confirming eligibility, the participants will finally be enrolled, and a treatment group will be assigned based on a pre-generated random assignment table. Randomization will be performed on three treatment groups at a 1:1:1 ratio: 24 cGy/6 fractions of LDRT, 300 cGy/6 fractions of LDRT, or sham RT. After allocation, patients will undergo CT simulation of the whole brain using personalized immobilization devices. Treatment planning will be performed using three-dimensional conformal RT.

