### Sample size calculation

This trial is intended to further evaluate the treatment effect of LDRT on AD, and it is difficult to calculate the appropriate effect size for the treatment and control groups. Therefore, the purpose of this study is exploratory, in the form of a pilot study to compare efficacy. Bonferroni correction will be performed, and a comparative, parallel, three-arm design will be adopted with 80% power and a 2-sided alpha of 0.05. Finally, 20 people per group, for a total of 60 people, is calculated as the number of samples considering the dropout rate.

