### Statistical analysis

Baseline characteristics according to the three groups will be compared using Student’s unpaired *T*-test or Wilcoxon’s rank sum test for continuous values. For categorical variables, the chi-squared test or Fisher’s exact test will be performed. A paired *t*-test or Wilcoxon’s signed test will be performed to evaluate the changes after 6 months from baseline in each group.

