To determine the daily dose for the experimental groups, we referenced an experimental paper on radiation dose-dependent hippocampus apoptosis in adult mice [24]. In this study, dose-response curves were linear-quadratic, with a significant relationship between the appearance of cell death and irradiation dose in the range of 0–2 Gy. Furthermore, in a recent review article on low dose ionizing radiation affecting the immune system, Lumniczky et al. divided daily doses into three groups based on the following ranges: low-doses (<100 mGy), intermediate-doses (100 mcGy to 1 Gy), and high-doses (>1 Gy). High-doses mainly have immunosuppressive and pro-inflammatory effects, while low-doses have sustained immunomodulatory and anti-inflammatory effects [25]. Based on these facts, we adopted two experimental daily doses less than 1 Gy. The determination of the irradiation dose in experimental group 1 was based on a case report by Cuttler et al. [9], which showed remarkable cognitive improvement through a total of 5 trials of approximately 40 mGy per brain CT scan. The dose in experimental group 2 was determined according to Yang et al. [6]. In this study, mice will be irradiated with a total dose of 300 cGy (5 fractions×60 cGy) to prevent the accumulation of Aβ plaques and alleviate cognitive decline. A daily dose of 200 cGy, which is currently used in other ongoing clinical trials, will not be used in this study because there was no therapeutic effect in the LDRT study at a daily dose of 180 cGy conducted by our research team as a pilot study (NCT04203121). A recent study by Rogers et al. showed promising results using a daily dose of 200 cGy, but it was a pilot study with only five patients, so the reliability of the daily dose cannot be determined [17]. To rule out a placebo effect, the control group will receive sham irradiation. Therefore, in this study, two experimental groups will be used: 4cGy per fraction (a total of 24 cGy/6 fractions) and 50 cGy per fraction (a total of 300 cGy/6 fractions) to verify the treatment effect compared with that in the control group (sham RT).

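### The trial has a dose aim, but no stated analysis estimates the difference between 24 and 300 cGy, so a split in significance between the arms could be read as a dose difference

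*Protocol article*

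**What the plan says.** **Aim.** Under Study design and registration, the article says the trial will assess safety and efficacy "in the whole brain of patients with AD and determine the potentially applicable radiation dose". The Introduction is softer and aims to "explore the appropriate LDRT dose per fraction and schedule". Sample size calculation describes the purpose as exploratory and pilot in form.

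**Design.** Baseline and randomization (Visit 2): "Randomization will be performed on three treatment groups at a 1:1:1 ratio: 24 cGy/6 fractions of LDRT, 300 cGy/6 fractions of LDRT, or sham RT". The two active totals differ 12.5-fold (300/24).

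**Analysis.** The Statistical analysis section uses between-group tests for baseline characteristics. Its one efficacy test is a paired t-test or signed-rank test "to evaluate the changes after 6 months from baseline in each group". The Discussion gives the purpose of the two doses as "to verify the treatment effect compared with that in the control group (sham RT".

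**Multiplicity and size.** Sample size calculation states: "Bonferroni correction will be performed, and a comparative, parallel, three-arm design will be adopted with 80% power and a 2-sided alpha of 0.05". It does not say which comparisons the correction covers. It adds "20 people per group, for a total of 60 people, is calculated as the number of samples considering the dropout rate", and says of the effect size that "it is difficult to calculate the appropriate effect size for the treatment and control groups".

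**Endpoints.** Outcome measures names two primary endpoints at 6 months: ADAS-K change and the number of adverse events. An improvement of at least 5% from baseline counts as a valid response. This rule classifies a response and does not choose between doses.

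Nowhere does the article state a contrast between the two doses, a dose-response test or a rule for choosing a dose.

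**The concern.** Separate tests, one per arm, do not test a difference between arms. This holds whether each dose is tested against its own baseline or against sham. If one dose reaches significance and the other does not, the natural report is that the first dose works and the second does not. Two equally effective doses can produce that pattern by chance, and with small arms they do so fairly often.

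This goes beyond detail that an article leaves to the analysis plan. The article states an aim and states analyses, and the stated analyses do not yield the quantity that the aim needs. Adding tests against sham would not close the gap, because the dose question would still turn on two separate p-values.

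**Working it through.** **Inputs.** From the article: three arms, 1:1:1, 20 per arm, two-sided alpha 0.05, 80% power, Bonferroni over an unstated number of comparisons. Assumed, because the article gives no values: the standardized effect (0.3 to 1.2 SD of the 6-month change), normal data, and both doses truly equal. Alpha is taken as 0.05, or 0.025 for two comparisons.

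**The plan's own figure.** The 20 per group cannot be reproduced without an effect size, SD or dropout rate. Working backwards, the difference detectable with 80% power is (z for alpha/2 + z for power) × √(2/n):
- alpha 0.05: (1.960 + 0.842) × √(2/20) = 2.802 × 0.316 = 0.89 SD
- alpha 0.025: (2.241 + 0.842) × 0.316 = 0.97 SD

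**Split probability, within-group tests.** The arms are independent, so P(exactly one significant) = 2p(1 − p), where p is the power of the paired t-test from the noncentral t with 19 df and noncentrality d√20. For d = 0.5 and alpha 0.05, noncentrality is 0.5 × 4.472 = 2.236 and p = 0.565, so the split is 2 × 0.565 × 0.435 = 49%.

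**Split probability, tests against sham.** The two tests share the sham arm (correlation 0.5), so the probability was simulated with a pooled SD on 57 df.

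| True effect (SD) | Sham, alpha 0.05 | Sham, alpha 0.025 | Within group, alpha 0.05 | Within group, alpha 0.025 |
|---|---|---|---|---|
| 0.3 | 19% | 13% | 37% | 27% |
| 0.5 | 30% | 25% | 49% | 49% |
| 0.6 | 33% | 30% | 40% | 48% |
| 0.8 | 28% | 32% | 14% | 24% |
| 1.0 | 16% | 22% | 2% | 5% |
| 1.2 | 6% | 10% | under 1% | under 1% |

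The effect means change from baseline in the within-group columns and difference from sham in the others, so the two pairs of columns are not on one scale.

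**At the stated 80% power per test.** Within group: 2 × 0.8 × 0.2 = 32%. Against a shared sham arm: about 23%.

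**What a split says about the doses.** In the simulated splits against sham (0.5–1.0 SD), a direct dose contrast is itself significant at 5% in only about 12–14%.

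**Overstatement of the better-looking arm.** For two equal arms, E[max] − truth = (1/√π) × (1/√20) = 0.564 × 0.224 = 0.126 SD.

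**Precision of a direct estimate.** Half-width of the 95% interval = t(57) × √(2/20) = 2.002 × 0.316 = 0.63 SD. With 16 evaluable per arm it is t(45) × √(2/16) = 2.014 × 0.354 = 0.71 SD. Power of a direct contrast at alpha 0.05 with 20 per arm is about 15% for a true dose difference of 0.3 SD, 34% for 0.5 SD and 69% for 0.8 SD.

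**The case against.** - **No selection rule is stated.** A reader might infer that the trial will pick its dose by which arm is significant, or that a wrong dose will go forward on noise. The article says neither. The aim is qualified by "potentially", the study is called exploratory, and nothing commits to taking a dose forward. Adverse events and the 5% response rule could also inform a dose statement. All of this stands, so the point is limited to efficacy-based dose statements drawn from the stated analyses.
- **The contrast may exist elsewhere.** A three-arm Bonferroni family could mean all pairwise comparisons, including dose against dose, and a fuller protocol or analysis plan may name it. This is possible, but the article does not say so, and its analysis section and Discussion point to other comparisons.
- **The percentages depend on assumed effects.** They do. Splits become uncommon when power is high, as the lower rows of the table show. At the stated 80% power they are still 23–32%.
- **The larger gap is the lack of any between-group efficacy test, even against sham.** This is correct, and the fix has to start there, since there is no sham-comparison model to which a dose contrast could simply be added.
- **A direct contrast would be imprecise.** It would. It also does not remove the 0.126 SD overstatement of the better-looking arm. This supports reporting an estimate with an interval and a more modest aim. It does not support leaving the dose difference unestimated.

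**Conclusion.** The point holds in limited form. The article sets a dose aim, and none of the analyses it states estimates the difference between the doses. If both doses are equally effective and 20 per arm are evaluable, one significant and one non-significant arm would appear in about 16–33% of trials against sham for effects of 0.5–1.0 SD, falling to 6–10% at 1.2 SD. With the within-group tests as written, the figure is 27–49% for changes of 0.3–0.6 SD, falling to 14–24% at 0.8 SD. These figures rest on assumed effects, normal data and alpha of 0.05 or 0.025.

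The article does not show that the dose will be chosen this way. It leaves that reading open and offers no estimate that would prevent it. The change is worth making and cheap. It does not put the conduct of the trial in question.

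**What to change.** 1. In Statistical analysis, state a between-group analysis of 6-month ADAS-K change across the three arms. Report from it the 300 minus 24 cGy difference with a 95% interval, as an estimate outside the Bonferroni family.
2. Add that any efficacy-based dose statement will rest on that interval, read alongside the adverse-event results, and not on which arm reaches significance.
3. In Study design and registration, change "determine" to "explore", in line with the Introduction. A half-width of about 0.63 SD, wider after dropout, can neither establish equivalence nor reliably separate the doses.

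The cost is a few sentences and one word. It needs no more patients and spends no alpha. The price is a more modest dose claim. If a fuller analysis plan already contains the contrast, the article only needs to be brought into line with it.

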**Fig. 1 jad-95-jad230241-g001:**
[figure not shown]
Schematic design of the clinical trial. AD, Alzheimer’s disease; K-MMSE, Korean-Mini-Mental Status Examination; CDR, Clinical Dementia Rating scale; PET, positron emission tomography; ADAS-K, Alzheimer’s disease assessment scale-Korea; CGA-NPI, Caregiver Administered-Neuropsychiatric Inventory; K-iADL, Korean Instrumental Activities of Daily Living; SUVR, standardized uptake value ratio; LDRT, low-dose radiation therapy.

### Recruitment and eligibility criteria

This trial is conducted jointly by three institutions: Kyung Hee University Hospital in Gangdong, Chungbuk National University Hospital, and SMG-SNU Boramae Medical Center. Among the patients with AD who visit the Department of Neurology of each institution, those who meet the inclusion criteria for this study are referred to the Department of Radiation Oncology. In addition, with content approved by the Institutional Review Board (IRB), we are promoting patient recruitment through in-hospital publicity and advertisements in newspapers and subways.

The inclusion and exclusion criteria are presented in Table 1. All the following criteria should be satisfied for the patients to be included in the study: 1) age between 60 and 85 years; 2) diagnosed with probable AD dementia based on the new diagnostic criteria for AD outlined by the National Institute on Aging and Alzheimer’s Association; 3) stable maintenance of general AD drug treatment (donepezil, galantamine, rivastigmine, or memantine) for more than 3 months; 4) amyloid accumulation in the brain confirmed by amyloid positron emission tomography (PET); 5) mild AD (score range of 13 to 24 on the Korean Mini-Mental State Examination [K-MMSE] or 0.5 or 1 on the Clinical Dementia Rating scale [CDR]); 6) ability to perform cognitive function tests and imaging tests without help of others; and 7) accompanied by a guardian who provides information on the patient’s overall status, cognitive function, and functional changes. Patients who meet any of the exclusion criteria will be excluded from the study. The major exclusion criteria are 1) previous history of radiation to the brain; 2) previous history of malignancy diagnosed within 5 years from the time of screening or currently being treated; 3) cognitive decline associated with drugs or neurological or neurodegenerative conditions, not AD; and 4) clinically significant and unstable mental illness. The exclusion criteria are presented in Table 1.

**Table 1 jad-95-jad230241-t001:** The inclusion and exclusion criteria for the clinical trial

Inclusion	Exclusion
Aged between 60 and 85 years	Previous history of radiation to the brain
Diagnosed with AD dementia based on the new diagnostic criteria for Alzheimer’s disease outlined by the National Institute on Aging and Alzheimer’s Association	History of seizure within the previous 10 years of the screening time
Stably maintaining the general AD drugs (donepezil, galantamine, rivastigmine, or memantine) for more than 3 months	Skin disease on the scalp
Amyloid accumulation in brain confirmed by Amyloid PET	Previous history of malignancy diagnosed within 5 years from the time of screening or currently being treated
Mild AD (score range of 13 to 24 on the K-MMSE or 0.5 or 1 on the CDR	Pregnancy or breastfeeding
Able to perform cognitive function tests and imaging tests	Subjects with cognitive decline associated with drugs or neurological / neurodegenerative conditions, not AD (i.e., drug abuse, vitamin B12 deficiency, thyroid dysfunction, stroke or other cerebrovascular conditions, Lewy body dementia, frontotemporal dementia, and head trauma).
Accompanied by a guardian who provides information on the subject’s overall status, cognitive function, and functional changes	Clinically significant, unstable mental illness (i.e., uncontrolled depression, schizophrenia, and bipolar disorder) within the last 6 months
Written informed consent was provided by the subject or the guardian to participate in this trial	Subjects whose brain MRI confirms evidence of: acute or subacute hemorrhage, prior macro hemorrhage (defined as > 1 cm in diameter, T2 sequence) or prior subarachnoid hemorrhage unless it can be documented that the finding is not due to an underlying structural or vascular abnormality, more than 4 microhemorrhages, cortical infarct (defined as > 1.5 cm in diameter, irrespective of anatomic location),>1 lacunar infarct (defined as > 1.5 cm in diameter), superficial siderosis, and history of diffuse white matter disease as defined by a score of 3 on the age-related white matter changes scale. Any finding that, in the opinion of the investigator, might be a contributing cause of the subject’s dementia, or pose a risk to the subject, or might prevent a satisfactory MRI assessment for safety monitoring are also included in the exclusion criteria
	Those who have other findings that are considered clinically important, and those who are judged by the researcher to be inappropriate for participation in this study.

AD, Alzheimer’s disease; PET, positron emission tomography; K-MMSE, Korean Mini-Mental State Examination; CDR, Clinical Dementia Rating scale; MRI, magnetic resonance imaging.

**Fig. 2 jad-95-jad230241-g002:**
[figure not shown]
The overall progress scheme of the clinical trial.

### Baseline and randomization (Visit 2)

Eligible patients will be assigned to three treatment groups (two experimental groups and one control group) by stratified block randomization using a random number table. The researcher will obtain consent and assign the screening number to each participant in order. After confirming eligibility, the participants will finally be enrolled, and a treatment group will be assigned based on a pre-generated random assignment table. Randomization will be performed on three treatment groups at a 1:1:1 ratio: 24 cGy/6 fractions of LDRT, 300 cGy/6 fractions of LDRT, or sham RT. After allocation, patients will undergo CT simulation of the whole brain using personalized immobilization devices. Treatment planning will be performed using three-dimensional conformal RT.

### Intervention/treatment procedures (Visits 3–8)

Eligible patients will begin receiving interventions within 21 days of the screening tests. The experimental groups will be irradiated twice per week for 3 weeks (a total of six times) according to the radiation dose determined for each group, and the control group will be irradiated with sham irradiation. Twice weekly treatments are to be administered every Monday and Friday. A linear accelerator with 6 MV energy will be used to deliver whole brain irradiation to the patients assigned to the experimental groups. The target volume includes the whole brain at the C2 level to cover the skull base sufficiently (Fig. 3). The first experimental group will receive 4 cGy per fraction with a total of 24 cGy of LDRT. The second experimental group will receive 50 cGy per fraction, with a total of 300 cGy of LDRT. The sham irradiation group will be identical to the experimental group in all respects, including CT simulation, RT schedule, set-up procedure, gantry location, and in-room duration (approximately 20 min). Neurological examination, vital signs, and adverse events will be evaluated at every visit for the intervention.

